**Protection of Data:**

Personal Health Information (PHI) will be strictly maintained following the Cyber Security Checklist for Protected Health Information issued by the University of Florida Office of IT Security Management. Once we have completed consenting, we will assign a randomly generated study identification (ID) number. Any collected PHI during the screening process will be kept secure at all times. The PI of the project will create a document linking participant study ID with the participant’s name, and contact information. This study ID document key will be kept in a locked file cabinet in the PI’s office. Electronic copies of this document will be kept on an encrypted drive in an encrypted folder on a server maintained by the department accessible only to department IT administrator authorized users through a password protected computer operating Truecrypt or Bitlocker encryption software. Only the PI ([name]) and student study coordinator ([name]) will have access to identifiable PHI. De-identified PHI may be shared with members of the study staff for data analyses as is appropriate.

Participants that expressed permission to contact, but were not eligible to participate in current or future therapeutic horticulture sessions will have their forms destroyed at the end of the study enrollment period.

**Data Preservation and Access:**

The data acquired in the project will include human participant data that require Institutional Review Board approval. All rules and regulations related to privacy (i.e., HIPPA) will be followed with specific regard to collected data.

The electronic data will be preserved in multiple on-site backups in the form of DVDs and RAID hard drive storage. Copies of the (de-identified, see other) electronic data will be preserved online on a departmental server storage space allocated to the Department of Environmental Horticulture. The contents of server storage space is automatically backed up daily, weekly, and monthly. Lost or corrupted data files can be retrieved from the data backup repository. Additional backup on external hard drives stored off campus will not be permitted. No local computer or mobile device will contain files of PHI or any sensitive information.

Original laboratory notebooks will be secured by the PI in his campus office. The data will be archived at the end of the project in the University’s institutional repository, a long-term digital archive containing scholarly or artistic work produced by researchers at the University of Florida.

Research data residing on a secured server will be accessible via VPN and Gatorlink password via the internet. The PI will transfer the research data from this proposed project to the data repository after completion of the research. If patents result from the research, the data will be embargoed until patents have been received. Otherwise, the data will be suppressed until all submitted papers have been published. Research data will be fully accessible for a period of time deemed relevant for the data, typically 5 years for the raw data described above, but not less than three years. Final products such as reports and published materials will be maintained indefinitely or for a period of at least 5 years. In the event the PI leaves the University, the data shall remain at UF for a period of 5 years.

De-identified raw data from the proposed research may be linked to published research article(s) as supplemental information. Data will, in principle, be available for access and sharing as soon as is reasonably possible, and not longer than four years after the acquisition of the data. As described above, the data will be retained for up to 5 years, exceeding the NSF guidelines to preserve the data at least three years beyond the award period, as required by NSF guidelines.

For long-term storage and archiving of analyzed data, the UF ResearchVault can be utilized. The ResearchVault is a secure computing environment that research data can be stored and archived. The ResearchVault is designed to store restricted data including:

• electronic protected health information (ePHI) (HIPAA)

• export-controlled data (ITAR/EAR)

• student data (FERPA)

• controlled unclassified information (CUI)

• intellectual property data (IP)

**Other Data Considerations:**

No significant intellectual property issues involved with the acquisition of the data are anticipated. In the event that discoveries or inventions are made in direct connection with this data, access to the data will be granted upon request once appropriate invention disclosures and/or provisional patent filings are made.

The data acquired and preserved in the context of this proposal will be further governed by the University Florida policies pertaining to intellectual property, record retention, and data management.

Possible Discomforts and Risks:

There is minimal potential from the GA and AA for discomforts and risks beyond what would be experienced while engaging in low exertion gardening or art at home. Participants are not expected to get too hot or too cold because of working in a greenhouse or conference center during the time of year the experiments would take place. There are no risks to participants greater than those individuals would experience in their daily lives at home. GA sessions will only take place after the safe entry period has been satisfied should any pesticides be used in the greenhouse to control pests or diseases during the course of the experiments. Plant materials in the greenhouse treated with pesticides will not be used for any edible purposes.

Plants selected for inclusion in this research study have been screened for potential hazardous properties, and only plants known not to be hazardous have been selected for use. Plants grown for use in the GA by the study group will be free of harmful or hazardous pesticide residues. All plant materials grown by the study group that may be consumed by the participants will be pesticide free, and grown in compliance with established safety standards and recommendations (USDA Food Safety Tips for School Gardens). Some plant materials that are purchased from supermarkets that may be consumed during the experiment may contain some level of pesticide residues that are found on commercially salable produce and fruits.

There is a possible risk of protected health information of participants to be disclosed to unauthorized individuals. The study team will keep electronic files with PHI on a server that can only be accessed by a password-protected computer available only to the PI and study coordinator and appropriately authorized for access by the departmental IT administrator. Paper copies with PHI will be held in locked file cabinets for protection in the PI’s office. Data from ineligible participants (“screening failures”) will be safely shredded upon completion of screening visit.

Possible Benefits:

There are some direct benefits to participating in this research. Participants who complete the gardening program will benefit from learning about the forms, characteristics, sensory features and uses for a variety of plants, plant propagation techniques, planting and cultivation techniques that may contribute to the enhancement of participants’ quality of life. Similarly, participants that complete the art program will benefit from learning about art activities that may also contribute to the enhancement of participants’ quality of life.

**Reimbursement of Participation Costs:** To defray the costs associated with transportation and parking, the study will offer compensation up to the amount of $60 in gift cards for each participant who attends at least six of the gardening sessions, with payments of $20 at visits 2, 6 and 10. Participants in the gardening program will also receive a plant guidebook (“Florida Gardener’s Handbook” by MacCubbin, Tasker, Bowden and Lamp’l, 2012; valued at $24.00 containing information about most of the plants used in the GA. Participants in the gardening program will also be able take home the containerized plantings and individual plants generated from the activities. Total value for take home items from the GAs is estimated at $100 per participant. The participants in the art program will also receive up to $60 compensation, with payments of $20 at visits 2, 6 and 10. Participants in the art program will also be able to take home any art projects they have worked on during the program and an art guidebook (“The Artist’s Handbook” by Ray Smith, 2009) valued at $16.00 containing information about art techniques similar to those learned in the AAs. The value for the take home items for the AAs is estimated at $100. All participants will be asked to a sign a receipt, and study staff will track monetary compensation during the course of the experiments.

Conflict of Interest:

The study team does not have any conflict of interests to disclose.

References:

Andrews, L.W. (2013). Minding the Body: Nine ways to relieve stress by gardening. Psychology Today. April 1, 2013. <http://www.psychologytoday.com/blog/minding-the-body/201304/nine-ways-relieve-stress-gardening> Accessed June 2, 2014.

ATUS 2003-2015. US Department of Labor, Bureau of Labor Statistics and US Department of Commerce, US Census Bureau. American Time Use Survey. <https://www.bls.gov/tus/datafiles_0315.htm>. Accessed June 27, 2017.

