**Study Sample Size:** Based on a set of power calculations from the previous gardening pilot study (IRB201400425), we estimate needing up to 20 individuals in each of the experimental conditions, i.e. gardening program and art program. We will consider the study fully enrolled when 40 study participants are deemed eligible and ready to participate in the experimental intervention. Based on power calculations of psychometric data from the previous gardening study, minimum estimated sample sizes range from 12 to 17 participants required for the gardening experimental condition to achieve sufficient power. However, it is anticipated that perhaps as many as 50% of consented volunteers may fail one or more eligibility requirements, or elect not to continue in the experimental stage of the study.

We anticipate over the experimental treatment duration, that some participants might experience a life event (illness, loss of a loved one, serious accident or similar occurrences) that makes it necessary for them to withdraw from the study prior to study completion. Others may simply decide to cease participating. Some participants may miss some of the sessions. We believe the study, if fully populated, can sustain a 20% attrition rate in either of the two treatment groups and still provide valuable scientific information. Study staff will keep records of participant attendance. We have arbitrarily set an attendance minimum of 6/8 GA or AA sessions for the inclusion of data from a subject. Participants that have a major life event or miss more than two sessions will be allowed to attend all remaining gardening or art sessions. However, no further data from a subject will be collected following the third missed gardening or art session. Any collected data from such participants will be flagged and excluded from data analyses as determined to be scientifically appropriate.

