**The Health and QOL Evaluations:** Gardening programs and horticultural therapy have been linked with reduced levels of anxiety, depression, pain, and stress, and lower heart rate, and improved cognitive function, self-esteem, physical and mental health and quality of life. Similarly, art programs and art therapy have been linked to improvements in positive and negative affect, anxiety, self-esteem, depression symptomatology, and quality of life (Uttley et al 2015). The impacts of the treatment regime on participants will be evaluated with several self-report assessment instruments that have been properly licensed or purchased. The standard SF-36 Health Survey instrument (Ware and Sherbourne 1992; Hays et al 1993) will be used to evaluate eight scales that link to physical and mental health over a four-week recall interval. To gain information relative to stress, the study will use the Perceived Stress Scale (PSS) (Cohen et al 1983) with a recall interval of one week. To gain insight relative to the intensity of depression, the study will use the Beck Depression Inventory 2^nd^ edition (BDI-II) (Beck et al 1988) with a recall interval of two-weeks. To gain information relative to anxiety, the study will use the State Trait Anxiety Inventory (STAI) instrument (Form Y) (Spielberger et al 1983). The STAI reports on *“at this moment”* status. The study will also use the POMS 2-A® short form instrument (McNair et al 1981; Shacham 1983) to assess the mood states of individuals in an effort to examine changes in mood during the course of the treatment. The POMS reports on *“at this moment”* status with regard to mood disturbance. The Profile of Mood States™ provides self-report scales that allow for the assessment of transient, fluctuating feelings, and enduring affect states. The tool is applicable in settings where sensitivity to change is needed to assess treatment progress monitoring and evaluation. The Satisfaction with Participation in Discretionary Social Activities (SPDSA) PROMIS short form v1.0 instrument will be used to assess contentment with participants’ leisure time and affairs with friends, and encompasses a recall interval of one week. The SF-36, PSS, BDI-II, STAI, POMS 2-A Short, and SPDSA instruments will be administered prior to the beginning and following the completion of the gardening and art sessions treatment regime during visits 2 and 11. In addition, for both the GA and AA groups the POM 2-A Short and PSS instruments will be administered on a weekly basis at the conclusion of the 2^nd^, 4^th^, 6^th^ and 8^th^ gardening and art sessions during visits 4, 6, 8 and 10 to provide a time-course of mood and stress status, respectively, during the experiment. The BDI-II will be administered at the conclusion of the 4^th^ and 8^th^ gardening and art sessions during visits 6 and 10 to provide information on the depression status during the experimental regime. Heart rate and blood pressure measurements will be made at the beginning and end of visits 2-11.

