
**Data Collection:** The study team will collect baseline data on each subject prior to the beginning of the gardening or art activity sessions by administering various assessments during the orientation session, visit 2. In a final wrap-up session, visit 11, we will repeat the data collection, administering the complete battery of assessments following participation in the 8^th^ and final activity session of the program. Assessments of the participants will be in the form of self-administered health-related questionnaires, a discretionary social activities questionnaire, and heart rate and blood pressure monitoring. Trained research study staff will administer questionnaires. Heart rate monitoring for each participant will be accomplished for each session by way of BP wrist cuff readings and heart rate monitoring with the Omron 7 monitor (BP and HR) wearable. Two to three measurements will be taken at the beginning and at the end of each session.

**Other Study Procedures:** If a study participant completes a health and psychometric assessment instrument, and the study staff sees that their responses indicate depressive or anxiety symptomatology, the study staff will recommend that the individual seek professional help.

**Incidental Findings:** No incidental findings are anticipated, but if an incidental finding is made, the participant will be given a direct referral for medical follow-up. The results from the medical follow-up and review will not be provided by the service to the PI.

Anytime a health and psychometric assessment instrument is completed and the study staff sees responses that indicate depressive or anxiety symptomatology, the study staff will recommend the participant seek professional help. In the event that evaluation of the BDI-II or STAI responses suggests a risk of self-harm or suicidal behavior by a study participant, a qualified mental health professional arranged by the study staff irrespective of day and time will immediately evaluate the individual. Study staff will assist as needed to access emergency care at a recognized mental health treatment facility.

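### No payment is attached to visit 11, the only post-treatment measurement of SF-36, STAI and SPDSA, and the six-session payment condition is written for gardening only and cannot be assessed at visits 2 or 6

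*Protocol*

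**What the plan says.** Under Reimbursement of Participation Costs, the gardening arm is offered gift cards worth up to $60 "for each participant who attends at least six of the gardening sessions, with payments of $20 at visits 2, 6 and 10". The stated purpose is to cover transport and parking. For the other arm the text reads "The participants in the art program will also receive up to $60 compensation, with payments of $20 at visits 2, 6 and 10", and no minimum number of sessions follows.

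The final outcome visit is set under Data Collection: "In a final wrap-up session, visit 11, we will repeat the data collection, administering the complete battery of assessments". The Health and QOL Evaluations section lists SF-36, PSS, BDI-II, STAI, POMS 2-A Short and SPDSA as given "prior to the beginning and following the completion of the gardening and art sessions treatment regime during visits 2 and 11". Three of these are also given during the programme. POMS and PSS follow the even-numbered "gardening and art sessions during visits 4, 6, 8 and 10 to provide a time-course of mood and stress status". BDI-II is given after session 4 and again after session 8, described as "gardening and art sessions during visits 6 and 10 to provide information on the depression status during the experimental regime". Every visit from 2 to 11 also includes readings of heart rate and blood pressure.

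Under Study Sample Size, the attendance rule for analysis covers both programmes: "We have arbitrarily set an attendance minimum of 6/8 GA or AA sessions for the inclusion of data from a subject".

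**The concern.** There are two separate issues.

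The first is timing. The last gift card is handed over at visit 10, and the wrap-up visit is one further trip with neither an activity session nor a payment. For SF-36, STAI and SPDSA, a woman who does not come to visit 11 has a baseline and nothing after treatment. These instruments matter to the stated hypotheses. SF-36 and STAI bear on the first (mental health and quality of life), and SPDSA is the only instrument for the second (satisfaction with discretionary social activities).

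The second is the attendance condition. Six sessions is also the minimum for a participant's data to be included. If the condition applies to gardening only, the arms are given different incentives to reach the threshold that decides who is analysed. That would be a post-randomisation difference unrelated to the content of the programmes. As drafted, the condition also cannot be assessed at two of the three visits where money is paid.

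**Working it through.** **Visit map.** The Health and QOL Evaluations section places sessions 2, 4, 6 and 8 at visits 4, 6, 8 and 10. So session s falls at visit s + 2. Visit 2 is orientation, visits 3 to 10 are sessions 1 to 8, and visit 11 is the wrap-up.

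**Can the six-session condition be assessed when money is paid?** The most sessions a woman can have completed by each payment visit are:

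| Payment visit | Sessions possible | Six reachable? |
| --- | --- | --- |
| 2 | 0 | No |
| 6 | 6 − 2 = 4 | No |
| 10 | 10 − 2 = 8 | Yes |

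The sixth session is visit 6 + 2 = 8. The condition can therefore act only on the visit 10 payment, which is $20 of the $60.

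**What depends on visit 11?**

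| Measure | Last value before visit 11 | Post-treatment value if visit 11 is missed |
| --- | --- | --- |
| SF-36, STAI, SPDSA | Visit 2 (baseline) | None |
| POMS, PSS | Visit 10, after session 8 | Visit 10 |
| BDI-II | Visit 10, after session 8 | Visit 10 |
| Heart rate, blood pressure | Visit 10, start and end | Visit 10 |

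The exposure is three instruments, not the whole battery.

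**Size of one loss.** Study Sample Size gives up to 20 per arm and a minimum of 12 to 17 for the gardening condition. It states no alpha, power, effect size or SD, so that range cannot be reproduced. For scale only, assume that 17 per arm gives 80% power in a two-sided 5% two-sample t-test. The noncentrality is d × √(n1·n2/(n1 + n2)) on n1 + n2 − 2 degrees of freedom. Solving for 80% at 17/17 gives d = 0.991. Then:

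- 20/20: 86.3%
- 20/19: 85.4%
- 20/18: 84.3%
- 20/17: 83.2%

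One woman missing from one arm costs 86.3 − 85.4 = 0.9 points, and three missing from one arm cost 86.3 − 83.2 = 3.1 points.

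If instead 12 per arm gives 80%, then d = 1.197. Power is 95.8% at 20/20 and 95.3% at 20/19, a loss of about half a point.

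**The case against.** The strongest case against is that this is a reimbursement clause with a drafting gap, not a design fault. Most of its parts stand.

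- **Timing is equal.** Both arms are paid at the same three visits. A reader might infer that the schedule itself produces arm-dependent loss; the protocol gives no support for that.
- **The missing art condition may be unintended.** The art sentence says those women also receive up to the same total on the same schedule, which suggests parallel terms. The consent pages are not in the copy reviewed, so the terms given to participants cannot be seen.
- **The rules on data are the same in both arms.** The 6/8 minimum covers both programmes, data collection stops after the third missed session in either, and anyone missing more than two sessions is dropped. Even on the literal reading, the asymmetry concerns one $20 card.
- **Visit 11 is not unique.** The in-person consent and screening meeting before visit 2 also has no session and no stated payment. That visit 11 is the one most likely to be skipped is a conjecture; no rate of missed visits is given.
- **The power figures are assumption-driven.** The 12 to 17 range comes from an earlier study with a no-treatment control and is stated for the gardening condition. The protocol does not show that it is a per-arm requirement for gardening versus art. It also says the study can tolerate 20% attrition in either arm, which is 4 of 20.

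Two things survive. SF-36, STAI and SPDSA do have their sole post-treatment value at a visit with no payment. And the payment condition as written names one arm and cannot be assessed at two of its three payment visits, whatever was intended.

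**Conclusion.** The point holds as a minor one, in two parts.

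First, the payment schedule leaves the only post-treatment SF-36, STAI and SPDSA values without any payment attached. This is an avoidable risk of missing data, equal in both arms and of unknown frequency. A reader might infer that every post-treatment measure is exposed; the visit 10 values of POMS, PSS, BDI-II, heart rate and blood pressure show otherwise.

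Second, the attendance condition is written for gardening only and cannot be assessed at visits 2 or 6. Taken literally, it gives the arms different incentives to reach the data-inclusion threshold. That this would make the analysed groups differ is possible but not shown, and the documents give no basis for any figure for a difference in retention between arms.

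On size, one loss in one arm costs about 1 point of power if 17 per arm gives 80%, and about half a point if 12 per arm does. A reader who steps down equal arm sizes, from 20/20 to 19/19 and so on, would see 2 to 3 points per step. Each such step removes a woman from both arms, so it overstates the cost of a single missed visit.

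**What to change.** Keep the $60 total and pay the last $20 at visit 11, on attendance for the final battery, so that payments fall at visits 2, 6 and 11. Replace the two payment sentences with one condition that applies identically to gardening and art and can be assessed at each payment visit, rather than a session count that cannot yet be known at visits 2 and 6. State in the same place what applies to a woman whose data collection has stopped after a third missed session, since she would not be due the final battery.

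The cost is a change to the protocol, and to the consent wording if it repeats these terms. No extra money is needed. The downside is that participants wait slightly longer for the last payment.
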